## Discussion

Previous studies have shown that psychosocial problems experienced by individuals undergoing genetic counseling for cancer are often left undetected and thus untreated. One way that has been proposed to address this problem is to make use of patient reported outcome (PRO) measures in routine clinical practice to first identify, and then to manage relevant psychosocial issues. Previous studies that have evaluated the efficacy of implementing PRO measures in clinical settings have shown an increase in communication about health-related issues and an increase in clinicians’ awareness of their patients’ problems and, to a lesser extent an improvement in patient management and health over time
[21-23,35]. To our knowledge, no previous studies have investigated the value of using such PRO data in daily clinical cancer genetic counseling.

This clinical trial will evaluate the efficacy of using a relatively brief, psychosocial screening questionnaire, the PAHC questionnaire, in improving communication about, recognition of, and management of psychosocial problems among individuals undergoing cancer genetic counseling and testing.

### Methodological issues

A major strength of the study is its use of a randomized design that will ensure high levels of internal validity. The relatively large sample size, the multicenter approach, and the heterogeneity of the study sample will increase the external validity and generalizability of the findings.

Several possible limitations of the study should also be noted. First, due to the nature of the intervention, it is not possible to blind the genetic counselors, nor the counselees, nor the raters of the audiotapes to group allocation. This carries with it the risk of contamination, particularly on the part of the counselors. That is, any given genetic counselor will be seeing both counselees assigned to the intervention group and the control group. Thus, it is conceivable that the counselors’ experience with the intervention (i.e., receiving personalized feedback regarding the counselees’ self-reported psychosocial problems) will also affect the way they interact with counselees in the conrol group. We would note, however, that any such carry over effect will have a conservative effect on the study (i.e., that, if anything, it will make it more difficult to observe significant group differences on the primary study outcomes). A second possible limitation of the study will depend on the observed prevalence of psychosocial problems among counselees. If the prevalence is low, then it will be more difficult to detect group differences in the various study outcomes. Finally, due to funding limits, the follow-up period for the second phase of the trial is relatively short (only 4 months).

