### Recruitment and randomization

All eligible counselees will receive an invitation letter from the family cancer clinic, an informed consent form, a baseline questionnaire, and a return envelope three weeks before their first counseling session. Upon returning the completed informed consent form and the baseline questionnaire, we will randomize the participants on a 1:1 basis to either the intervention group or the control group. The minimization method will be used to balance the intervention and control group for each counselor in terms of gender and the cancer syndrome for which genetic counseling is requested
[28]. Neither the counselees nor the counselors will be (or can be) blinded to group assigment.

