The results of the PAHC questionnaire + DT will be printed and attached to the counselee’s medical record so that they are available to the genetic counselor prior to the relevant counseling session (face-to-face in phase I and telephone-based in phase II). To facilitate the genetic counselor’s rapid review of the questionnaire output, all problem domains for which the counselee responds “quite a bit” or “very much” to at least one item are color coded *red*, indicating a problem area that should preferably be discussed during the counseling session. All other problem domains, are color coded *green*, indicating that there is, in principle, no need to discuss it during the counseling. Additionally, based on the literature and analysis of a validation of the DT in a previous study by our group using a heterogeneous sample of counselees for cancer in the Netherlands, a score of 4 or greater on the DT is used to indicate a clinically relevant level of distress
[25,29]. Finally, the counselor will receive information about whether the counselee is interested in obtaining additional professional psychosocial support for any given problem area. Scores on the DT above the cut-off point, and counselees’ requests for additional psychosocial support are also color coded *red.* Additionally, to increase the ease of interpretation of the results, all items above the threshold will be printed in a bold font, and those items that are not above the threshold will be printed in light-grey. All counselors will receive written instructions/guidelines and training in the use of the PAHC questionnaire and the DT.

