### Control group procedure

Counselees in the control group will complete the PAHC questionnaire and DT as described above for the intervention group. However, the results of these questionnaires will not be provided to the genetic counselors.

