#### Discussion of psychosocial problems

Counselor-counselee communication about psychosocial issues will be assessed via content analysis of the audiotaped counseling sessions. Using a study-specific questionnaire, each counseling session will be coded for the specific psychosocial issues discussed during the counseling session. The coding reflects the 26 psychosocial issues of the PAHC questionnaire. Additionally, the percentage of counseling time devoted to the discussion of psychosocial issues will be calculated.

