### Secondary outcome measures

Secondary outcomes include: (1) initiation of problem discussion; (2) the time devoted to discussing each psychosocial problem and the total duration of the counseling session; (3) cancer worries and general psychological distress; (4) cancer genetics-specific psychosocial problems; and (5) counselees’ and counselors’ satisfaction with the genetic counseling and with the intervention (the latter for the intervention group only).

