### Statistical analyses

All analyses will be performed on an intention-to-treat basis. Missing data on the HADS and CWS will be imputed using half-scale mean substitution methods. Data of participants who complete and return their first follow-up questionnaire after their final counseling session will be omitted from the analysis, because knowing the DNA-test result might influence questionnaire responses. Between rater agreement on the audiotaped sessions will be assessed by calculating the percentage of absolute agreement. Effect sizes will be calculated using standard statistical approaches.

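### The plan calls masking of the audiotape raters impossible, though nothing it describes requires them to know the arm, and it checks their coding by raw percent agreement only

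*Protocol article*

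**What the plan says.** Two places in the protocol article deal with blinding. Recruitment and randomization speaks of two groups only: "Neither the counselees nor the counselors will be (or can be) blinded to group assigment". Methodological issues adds the raters: "it is not possible to blind the genetic counselors, nor the counselees, nor the raters of the audiotapes to group allocation". The only consequence it then discusses is contamination, meaning that counselors carry the habit of using the feedback into control sessions. It correctly notes that this would make a difference between arms harder to show.

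The arms differ in what the counselor receives. Both complete the questionnaire, but for controls "the results of these questionnaires will not be provided to the genetic counselors". In the intervention arm the counselor has a color-coded printout, with red "indicating a problem area that should preferably be discussed during the counseling session".

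For the first primary outcome, "Counselor-counselee communication about psychosocial issues will be assessed via content analysis of the audiotaped counseling sessions", using the 26 questionnaire issues as the coding frame. Referral, part of the third primary outcome, is coded from the same tapes. Under Timing and content of study measures, 10% of sessions are double-coded, split equally between the arms. Under Statistical analyses, "Between rater agreement on the audiotaped sessions will be assessed by calculating the percentage of absolute agreement". No other statistic is named for the tape coding.

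**The concern.** Deciding whether a stretch of conversation counts as one of 26 psychosocial issues is a judgment. A rater who knows that the counselor had the printout may hear more issues, or credit more to the counselor. That bias favors the intervention, the opposite direction from the contamination that the protocol discusses. It would act on the outcome that sets the sample size, on coded referral, and on the secondary outcomes of who initiated a topic and how long it was discussed.

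A second and separate weakness lies in the reliability check. Percent absolute agreement is not corrected for chance. If issues are seldom discussed, two raters will mostly agree on absence, and the figure can look good while agreement on what was actually discussed is poor.

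**Working it through.** **Inputs from the protocol article.** Power 0.80, alpha 0.05, d = 0.4, 99 per arm, 198 in total, 25% without a second session, 264 recruited (Sample size and power calculations); 26 issues (Discussion of psychosocial problems); 10% double coding, balanced by arm (Timing and content of study measures). **Assumed, because the documents give no figures:** the size of a rater shift and how often each issue is discussed.

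**1. Does any step need raters to know the arm?** The intervention is a printout placed in the record for the counselor before the session. The raters' material is the recording. Coding issues, initiation, time and referral uses only what is said. The arm-balanced double-coding sample needs the allocation list, but another person can draw it. The tape itself can reveal the arm when the counselor refers to the results. That makes masking incomplete, not impossible.

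**2. The plan's own figure.** n per arm = 2(1.960 + 0.842)² / 0.4² = 98.1, rounded up to 99. Then 2 × 99 = 198 and 198 / (1 − 0.25) = 264. The stated numbers reproduce, taking alpha as two-sided, and there is no error here.

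**3. What a rater shift would do.** Suppose there is no true effect and knowledge of the arm shifts the coded count by b SD. With SE = √(2/n), the rejection probability is 1 − Φ(1.96 − b/SE) + Φ(−1.96 − b/SE).

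| Assumed shift b | 99 per arm (SE 0.142) | 132 per arm (SE 0.123) |
|---|---|---|
| 0.1 SD | 10.8% | 12.8% |
| 0.2 SD | 29.1% | 36.9% |

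The nominal rate is 5%. The two shifts are a quarter and a half of the design effect of 0.4.

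**4. Agreement by chance.** If both raters code an issue present with probability q, independently, they agree with probability q² + (1 − q)². Kappa is (observed − chance) / (1 − chance), shown here for an observed agreement of 85%.

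| Assumed q | Chance agreement | Kappa at 85% |
|---|---|---|
| 10% | 82% | (0.85 − 0.82)/0.18 = 0.17 |
| 20% | 68% | (0.85 − 0.68)/0.32 = 0.53 |
| 50% | 50% | (0.85 − 0.50)/0.50 = 0.70 |

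At q = 5%, chance agreement alone is 90.5%. The same reported 85% can thus mean poor or good coding, depending on a prevalence that the article does not give.

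**5. What the double-coded sample can support.** 10% of 264 is about 26 first-session tapes, or 13 per arm; 10% of 198 is about 20 telephone tapes. The chance that an issue never occurs in 13 tapes is 0.95¹³ = 51% at 5% prevalence and 0.90¹³ = 25% at 10%, and kappa for that issue may then be undefined. The sample supports a pooled statistic and an ICC for the count, not a kappa for each issue by arm.

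**The case against.** The protocol gives a reason for its statement and discloses the lack of blinding as a limitation. A counselor steered by a red-coded printout may well mention it, and if that is common, silence about the questionnaire hints at the control arm. This stands as a limit on how far masking can go. A reader might infer that raters could be largely masked; the documents do not say how many tapes reveal the arm, so that is not shown. It remains true that withholding the list removes the knowledge that the tape itself does not supply.

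A reader might also infer that counselees could be kept unaware of their arm until the first questionnaire is in, since "Counselees in the control group will complete the PAHC questionnaire and DT as described above for the intervention group". The article does not say when they learn it, and consent material is not shown. The session may reveal the arm before the questionnaire is repeated for the telephone call. No direction of bias in their answers can be derived either. That reading is not supported as a finding.

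On reliability, the low prevalences are assumptions, and the article does not say whether agreement is counted per issue or per session. At 50% prevalence, 85% agreement corresponds to a kappa of 0.70, which is acceptable. Prevalence-adjusted kappa is no way out: 2 × 0.85 − 1 = 0.70 at any prevalence merely rescales percent agreement. Nor can a chance-corrected statistic detect a bias that both raters share, since raters leaning the same way still agree.

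**Conclusion.** The concern holds for the raters. The blanket statement under Methodological issues is not supported by the procedures the article describes, and it forgoes a cheap safeguard on primary outcome 1 and the coded referral in primary outcome 3. The bias left open can favor the intervention and is not discussed. Its size is unknown: the false-positive rates of 10.8% and 29.1% show sensitivity to assumed shifts of 0.1 and 0.2 SD and do not predict what will happen. Primary outcome 2 compares the counselor checklist with counselee answers and is untouched by rater masking.

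The agreement statistic is a smaller, separate weakness. It matters if issues are rarely discussed, which the article neither states nor excludes. The planned sample size is unaffected by either point.

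**What to change.** In Methodological issues, replace the statement about raters with a rule:

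- Tapes carry a study number only, and raters are not given the allocation.
- Someone other than the raters draws the arm-balanced 10% double-coding sample.
- Raters record for each tape whether its content revealed the arm, and the unmasking rate is reported by arm.
- Any analysis limited to tapes that did not reveal the arm is labeled exploratory. It selects on an event after randomization that the intervention itself affects: intervention tapes where the printout goes unmentioned are plausibly those where it was used least.

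The same section should acknowledge that remaining rater bias could favor the intervention.

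In Statistical analyses, keep percent agreement and add, on the tapes already double-coded, an ICC for the number of issues discussed (the quantity analyzed) and a chance-corrected agreement pooled over issues and arms. This checks coding quality; it does not address a bias shared by both raters.

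The cost is file handling, one form item and two further statistics, with no extra tapes, raters or participants. The drawback is that masking will be only partial.

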## Conclusion

If proven efficacious, the introduction of a standardized procedure for assessing the psychosocial problems and needs of individuals undergoing cancer genetic counseling and testing will be a welcome addition to current clinical practice. It will facilitate timely discussion, detection and treatment of psychosocial issues specific to the cancer genetics setting. This is particularly important given the fact that the number of requests for genetic counseling is expected to continue to increase in the future. This will place additional demands on the time and resources of genetic counselors. Tools that facilitate early detection and treatment, or referral of those with specific psychosocial problems and concerns, are welcome.
